### Randomization process

We will use the CTCs as the unit of randomization. A total of 32 CTCs provide care and treatment to about 1,800 HIV-positive children aged 0 to 14 years old in Tanga. We will exclude private CTCs, as well as CTCs with less than 20 HIV-positive children. A total of 16 CTCs in the area are public and have at least 20 HIV-positive children receiving care and/or treatment; they also represent all the districts of the region. Of the 16 CTCs, 4 are from the Tanga urban area; this is due to a high number of CTCs and HIV-positive patients attending them. All CTCs based in district hospitals will be selected in this study because they fulfill the selection criteria. These 16 CTCs will be eligible for the randomization process: a coin toss to assign 8 CTCs to the intervention arm and 8 to the control arm. A person who is not a member of the study research team will conduct the randomization process.

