### Study design

We will conduct a cluster randomized controlled trial in Tanga, Tanzania. We will select 16 CTCs out of 32 for this study (Figure 1). The selected CTCs are located in public health facilities and have at least 20 enrolled HIV-positive children. We will use the coin-flipping method to randomly assign 8 CTCs to the intervention arm and 8 to the control arm (Figure 1). We will examine the effectiveness of nutrition training of MLPs on their nutrition knowledge, management of undernutrition, feeding practices, and the nutrition status of HIV-positive children attending CTCs. The intervention follows formative research conducted using focus group discussions and a cross-sectional study to examine factors associated with undernutrition, available foods, and local feeding practices for the children in this population. Results of the formative research are in the process of being published in another journal.

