#### HIV-positive children

We will recruit HIV-positive children attending the selected CTCs. Inclusion criteria for participation of the HIV-positive children are: aged 6 months to 14 years; registered or transferred to the CTCs; attended with his/her caregiver; consent by the caregiver to voluntarily participate in the study. We will exclude children whose ART information is missing in the medical records and whose HIV sero-status has not been confirmed. An estimated 800 children currently attend the 16 selected CTCs. Because half of the CTCs will be selected for the intervention arm, approximately half of the potential participants (400) will be in the intervention group and a similar number for the control group.

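### The stated coin toss does not by itself guarantee 8 v 8 CTCs, and it leaves the known urban location of 4 of the 16 CTCs to chance; a single stratified draw would settle both

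*Protocol article*

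**What the plan says.** The Randomization process section makes the CTC the unit of allocation: "We will use the CTCs as the unit of randomization". It describes the eligible set as follows: "A total of 16 CTCs in the area are public and have at least 20 HIV-positive children receiving care and/or treatment". The method is "a coin toss to assign 8 CTCs to the intervention arm and 8 to the control arm". The Study design section repeats it: "We will use the coin-flipping method to randomly assign 8 CTCs to the intervention arm and 8 to the control arm". The Abstract also gives both the coin and the 8 and 8.

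On what is known about the CTCs beforehand, the Randomization process section states "Of the 16 CTCs, 4 are from the Tanga urban area" and links this to the high number of CTCs and patients there. On size, the document gives a floor (CTCs "have at least 20 enrolled HIV-positive children") and a total of about 800 children across the 16, but no size for any single CTC. From the equal split of CTCs, the section on HIV-positive children infers that "approximately half of the potential participants (400) will be in the intervention group and a similar number for the control group".

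On who allocates: "A person who is not a member of the study research team will conduct the randomization process".

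**The concern.** The plan fixes both a mechanism and a result, and the mechanism does not by itself produce the result. Independent tosses give a random number of CTCs per arm. To reach 8 v 8 some further rule is needed, and none is given. The simplest rule is to toss down a list until one arm is full and send the rest to the other arm. That makes the joint allocation depend on how the list is ordered.

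The second issue is balance. With only 16 clusters, one cluster-level feature can easily line up with the training. Urban location is the feature that the protocol itself singles out, and it is known before allocation, yet the procedure does not use it. The Data analysis section promises adjustment for confounding variables, but the covariates listed under Measurements and HIV CTC related data do not name urban location. If all four urban CTCs fell in one arm, that arm would hold every urban clinic and adjustment would rest on thin information. Allocation happens once, so the time to deal with this is beforehand. The Trial status section says that the trial was still being formulated.

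**Working it through.** **Inputs.** 16 eligible CTCs, 8 per arm, 4 urban and therefore 12 other (Randomization process); about 800 children in the 16 CTCs (HIV-positive children), so a mean of 800/16 = 50.

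**1. Does tossing give 8 v 8?** With one fair toss per CTC, the number in the intervention arm is Binomial(16, 0.5).
- P(8 v 8) = C(16,8)/2^16 = 12,870/65,536 = 19.6%. The stated split is missed 80.4% of the time.
- One toss per pair of CTCs would give 8 v 8 every time, but no pairing is stated.

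**2. Toss until one arm has 8, then fill the other.** Let R be the number of CTCs placed without their own toss.
- P(R) = 2 × C(15−R, 7) × 0.5^(16−R), for R = 1 to 8.
- For R = 1, 2, ..., 8 this gives 20.9%, 20.9%, 19.3%, 16.1%, 11.7%, 7.0%, 3.1% and 0.8%.
- The mean of R is 3.14. R is at least 1 always, at least 2 with probability 79.1%, and at least 4 with probability 38.8%.
- An allocation settled after T tosses has probability 0.5^T. One settled at toss 8 has probability 1/256; one settled at toss 15 has 1/32,768. Under an equal-probability draw every allocation has 1/12,870.
- By symmetry, each CTC still has a one-half chance of each arm. A simulation of 100,000 sequences gave marginal proportions of 0.498 to 0.503 at all 16 list positions.
- The last four listed CTCs share an arm exactly when R is at least 4, so 38.8% of the time. For any four CTCs under an equal-probability draw the figure is 7.7%. This contrast concerns the urban CTCs only if they are listed last, which is an assumption.

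**3. Urban split under a proper unstratified draw of 8 from 16.** P(k urban in the intervention arm) = C(4,k) × C(12,8−k)/C(16,8).
- 2:2 — 43.1%
- 3:1 either way — 2 × 24.6% = 49.2%
- 4:0 either way — 2 × 3.85% = 7.7%

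**4. Stratified draw.** Choosing 2 of 4 urban and 6 of 12 other CTCs leaves C(4,2) × C(12,6) = 6 × 924 = 5,544 equally likely allocations, all 8 v 8 overall and 2:2 for urban.

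**5. Children per arm (illustrative).** CTC sizes are not given, so their coefficient of variation (CV) is assumed. For a draw of 8 from 16, the SD of an arm's total is sqrt(8 × S² × (1 − 8/16)) = 2S, with S = 50 × CV. The range is 400 ± 1.96 × 2S.
- CV 0.3: 341 to 459
- CV 0.5: 302 to 498
- CV 0.7: 263 to 537

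**The case against.** The strongest reply is that an article condenses its protocol. The tosses may be made within pairs or down a randomly ordered list, and either would remove the difficulty in step 2. An unstratified draw is a valid randomization whose chance imbalance is allowed for in the inference. Adjustment for confounders is planned, and no passage shows that urban location predicts the outcomes.

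Much of this stands. The missing stratification is a design weakness, not an error. The 38.8% v 7.7% contrast needs a particular list order that the document does not give. What does not stand is that the point is merely an omitted detail: the method is named in three places, always with an exact 8 v 8, and as named it does not deliver that result.

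Three stronger readings are tempting and should not be drawn:
- A reader might infer that coin tossing cannot give 8 v 8. It can, by chance 19.6% of the time or always with pairs. It is simply not guaranteed.
- A reader might infer that forced final placements break concealment. All 16 CTCs are identified before tossing and an outside person allocates, so the document shows no one able to act on a foreseeable assignment.
- A reader might infer that the arms will be too small because CTC sizes differ. The text promises only approximate equality, and even at an assumed CV of 0.7 the lower limit of 263 exceeds the stated minimum of 192 per arm.

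**Conclusion.** The point holds in a limited form. The stated mechanism does not guarantee the stated 8 v 8: independent tosses give it 19.6% of the time. Under the stop-at-8 rule, about 3 last-listed CTCs on average have no toss of their own and the allocations are not equally likely, while each CTC's own chance stays at one half. These figures are exact for fair tosses, but they describe two different possible procedures, and the document does not say which, if either, is meant.

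Separately, leaving urban location out means a 2:2 split only 43.1% of the time and complete separation 7.7% of the time, even with a correct draw. These figures need only the stated counts of 16, 8 and 4. How much an uneven split would matter depends on how strongly urban location relates to the outcomes, which the document does not show. The arm-size ranges are illustrative only. This is an improvement worth making before allocation, not a fault that invalidates the design.

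**What to change.** In the Abstract, the Study design section and the Randomization process section, replace the coin toss with one random draw, by computer or sealed lots, made by the same person outside the research team. Stratify it by urban location: 2 of the 4 urban CTCs and 6 of the 12 others go to intervention, and the rest to control. If enrolled numbers per CTC are available, the draw may also be constrained on size; this is optional. In the Data analysis section, include the urban stratum in the models that compare the arms.

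The cost is revised wording, slightly more work at allocation and one cluster-level term in the model. For an analysis at CTC level that term takes the degrees of freedom from 16 − 2 = 14 to 13. If stratification is not wanted, a plain draw of 8 from 16 (12,870 equally likely allocations) still secures the 8 v 8 split but leaves the urban balance to chance.

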### Measurements

#### Nutrition status

We chose the nutrition status of HIV-positive children as the outcome variable, including use of the categories underweight, wasting, and stunting. We will measure children’s weight using a standardized hanging Salter® scale (UK) calibrated to 0.1 kg for children who cannot stand and a standardized Seka® digital scale (Brooklyn, USA) for children who can stand. Height will be measured for children aged 24 months and older using a Seka® measuring rod calibrated to 0.5 cm [22]. We will use a designated mark on a board to measure lengths of children younger than 24 months in a recumbent position [23].

After obtaining height and weight data, we will convert them to a height-for-age z-score, weight-for-age z-score, and weight-for-height z-score [24] using the Epi-Info ENA Ver. 3.5.1, 2008 (CDC, Atlanta, Georgia, USA) software and WHO reference values [25,26]. Low height-for-age, weight-for-height, and weight-for-age are measures of stunting, wasting, and underweight, respectively [27].

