## Methods/Design

### Study area

We will conduct this study in HIV Care and Treatment Centers (CTCs) in Tanga, in the North Eastern region of Tanzania. Tanga is a coastal region with varied climatic conditions that allow diverse food production. Even if sisal market exports are lost, Tanga remains one of the main producers of cereals and fruits, and these make up a large part of its major economic activities.

Tanga is a food secured region; however, it has an unacceptably high proportion of child undernutrition. For example, in the nationally representative survey in 2010, more than 49% of the 315 under-five children surveyed in the Tanga region were stunted [2]. Acute undernutrition among them is also rampant; about 12% of the 315 under-fives were underweight while 5.5% were suffering from wasting. The regional diversity in food production does not reflect diversity in consumption. For example, Tanga produces various cereals, fruits, vegetables, and both fresh and sea water products; however, only 59.4% of the 292 children aged 6 to 60 months sampled from the general population consumed foods rich in vitamin A [14]. The proportion of vitamin A deficiency among these children was 38.9%, iron deficiency was 36.5%, and iron deficiency anemia was 52.2% [14].

The region is also not spared by HIV/AIDS epidemic. The prevalence of HIV/AIDS in the region is estimated to be 2.4%, based on a sample of 833 adults aged 15 to 49 years old who were tested as part of a nationally representative survey [15,16]. Data of nutrition profiles of HIV-positive children in this region is not available.

CTCs are specialized clinics to care for HIV-positive people, including children. They operate under vertical HIV programs and are integrated into the existing health infrastructure [17]. In Tanga, all CTCs are located in health facilities. They provide care and treatment to HIV-positive people including voluntary counseling and HIV testing, prescribing and dispensing ART, ART adherence counseling, diagnosis and treatment of opportunistic infections, monitoring response to treatment and disease progression, behavior change promotion, and outreach services, among others [15,17]. HIV-positive people attend CTCs every month to get ART refills. In each visit, they also receive adherence counseling and monitoring, examination by clinicians, and management of opportunistic infections, if any [15,17].

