### Data analysis

We will analyze the data based on the intention-to-treat principle. We will use both descriptive and regression analyses. For the descriptive analyses, we will conduct both χ^2^ and Student’s *t*-tests to examine the differences in characteristics of participants in the intervention and control groups. This study will have two types of outcome variables. First, nutrition status measured as underweight, wasting, and stunting. Second, feeding practices measured by feeding frequency, dietary diversity, and the quality and quantity of foods consumed. We will use multiple logistic regression analyses to examine the effectiveness of nutrition training on nutrition status and feeding practices of the two arms while adjusting for confounding variables. We will also conduct analyses to see monthly changes in feeding practices and nutrition status and to compare the intervention and control arms. To examine the independent association of nutrition counseling by trained MLPs on outcome variables, we will use repeated measures of ANOVA and Generalized Estimated Equation.

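### Wasting and underweight are defined by one set of z-scores for ages 6 months to 14 years, with no age or height band and no index for older children; if the WHO references end earlier, wasting describes only the younger children

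*Protocol article*

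**What the plan says.** The eligibility section on HIV-positive children admits those "aged 6 months to 14 years; registered or transferred to the CTCs". The Nutrition status section then defines the outcome: "We chose the nutrition status of HIV-positive children as the outcome variable, including use of the categories underweight, wasting, and stunting". It gives one conversion for everyone, "we will convert them to a height-for-age z-score, weight-for-age z-score, and weight-for-height z-score", to be done "using the Epi-Info ENA Ver. 3.5.1, 2008 (CDC, Atlanta, Georgia, USA) software and WHO reference values", and it links index to outcome: "Low height-for-age, weight-for-height, and weight-for-age are measures of stunting, wasting, and underweight, respectively". The Data analysis section repeats the outcome as "nutrition status measured as underweight, wasting, and stunting".

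The same section does set an age rule for measurement: recumbent length below 24 months, height from 24 months. It sets none for the indices. Nowhere does the article give the edition of the WHO reference or its limits, an index for older children, or the handling of a child for whom a z-score cannot be computed. It also gives no age distribution.

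**The concern.** A z-score exists only where its reference has values. The protocol applies three indices to an age span of about 14 years as if each reference covered all of it. If weight-for-height stops in early childhood, the stated rule yields no wasting value for most older children. If weight-for-age stops before 14 years, the oldest children have no underweight value either.

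The article calls stunting a chronic form of undernutrition (Background) and groups underweight and wasting as acute (Study area). In a trial with six months of follow-up, the acute outcomes are the ones more likely to move. Under such limits, stunting would be the only one of the three nutrition outcomes available for every child. The wasting result would answer a question about younger children while being presented as the result for the enrolled population. Children who pass a limit during follow-up would also lose the outcome partway through the monthly series. An index chosen for the older children after the data are seen would invite selective choice.

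**Working it through.** **The plan's own figure.** The documents state no number of children evaluable for wasting or underweight, so there is nothing to reproduce on this point.

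**Inputs from the protocol article**
- Age at entry: 6 months to 14 years (HIV-positive children). The upper end is taken as 14.0 years, or as 15.0 if children aged 14 are eligible until their next birthday.
- Recruitment: 400 per arm (Sample size estimation).
- Follow-up: 6 months (Follow-up).

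**Assumptions not in the documents**
- Weight-for-height ends at a height usually reached at about 5 to 7 years.
- Weight-for-age ends at about 10 years. This one is held less firmly.
- Ages at entry are spread evenly over the eligible range.

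**Formula.** Share computable = (limit − 0.5) / (upper age − 0.5). The denominator is 14.0 − 0.5 = 13.5 or 15.0 − 0.5 = 14.5. The number per arm is 400 × share.

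| Outcome | Assumed limit | Upper age 14.0 | Upper age 15.0 |
|---|---|---|---|
| Wasting | 5 years | 4.5/13.5 = 33%, 133 per arm | 4.5/14.5 = 31%, 124 per arm |
| Wasting | 7 years | 6.5/13.5 = 48%, 193 per arm | 6.5/14.5 = 45%, 179 per arm |
| Underweight | 10 years | 9.5/13.5 = 70%, 281 per arm | 9.5/14.5 = 66%, 262 per arm |

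**Without choosing a limit.** If a share f of children lies beyond a limit, 400 × (1 − f) per arm remain: 360 for f = 10%, 280 for 30%, 200 for 50% and 120 for 70%.

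**Crossing a limit during follow-up.** Six months is 0.5 years, so the share of all children crossing a given limit is 0.5/13.5 = 3.7% or 0.5/14.5 = 3.4%. That is about 14 to 15 of 400 per arm for each limit.

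**The case against.** The strongest reply is that the decisive premise is not in the documents. The article cites WHO reference values without edition or limits, and two references are cited that might together cover older children. That stands: the limits are an assumption, and a flat statement that the outcomes cannot be computed would go too far. What needs no assumption is that the stated rule has no band and no alternative index over the full enrolled range.

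A second reply is that age-specific handling belongs in a full protocol or analysis plan that is not shown. This has some force for the treatment of missing z-scores. It has less for the outcome definition, which the article states without qualification.

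Several stronger readings are tempting, and the documents do not support them:
- A reader might compare 124-193 per arm with the plan's minimum of 192 and call the wasting analysis underpowered against the plan's own standard. That minimum was derived for a 0.3 kg difference in weight gain, which needs no reference. It is not a threshold for wasting or underweight.
- A reader might infer that intention-to-treat is broken. A restriction by baseline age is independent of arm. It narrows the population described but does not disturb comparison by assigned arm.
- A reader might take the regional survey as proof that these indices are for under-fives, since "more than 49% of the 315 under-five children surveyed in the Tanga region were stunted". That shows who was surveyed, not where a reference ends.
- A reader might expect the software to return off-reference values. Nothing in the article says how it behaves.

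It is also fair that a height limit binds by height, not age. In a population with much stunting, children may stay below it longer, which is why the range runs to 7 years.

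**Conclusion.** The point holds in a conditional form. It is certain from the text that wasting and underweight are defined over 6 months to 14 years by weight-for-height and weight-for-age alone, without a band or an index for older children. Whether children lose these outcomes depends on reference limits that the article does not give and that must be checked against its cited references and the named software.

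If the assumed limits hold and ages are spread evenly, roughly half to two thirds of children would have no wasting value and about 30-34% no underweight value. Underweight is thus affected less, and less certainly. The true shares depend on the age distribution at the clinics. The consequence is a wasting result that describes the younger children only, plus a loss partway through follow-up in about 3-4% of children at each limit. The analysis by assigned arm and the sample size for weight gain are not put in question.

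**What to change.** In the Nutrition status and Data analysis sections:

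1. Name the edition of the WHO reference and the age and height limits of each index.
2. Define the acute index over the whole enrolled age range. Either use weight-for-height z in young children and BMI-for-age z beyond its limit, or use BMI-for-age z throughout.
3. Restrict weight-for-age (underweight) to the ages its reference covers, and say that the result applies to those ages.
4. Fix each child's index by age at baseline, so that it does not change during the six months.

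The cost is wording and reference tables. BMI uses the weight and height already collected, so no new measurement is needed. The downside is small: with two indices, the wasting outcome mixes measures across ages; with BMI-for-age throughout, it loses direct comparability with survey figures for under-fives. The change should be made before data collection begins.

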#### Dietary diversity

Dietary diversity is one of the measures of feeding practices and thus is one of our outcome variables. We will calculate a total dietary diversity score from a recalled list of food items consumed over the previous day. We will use a set list of 12 main food items found to be common in the formative research and the child questionnaire of the Tanzania Demographic and Health Survey [2,28]. We adopted this method as it has been used in previous studies among HIV-positive children in Tanzania [3,20].

#### Feeding frequency

Feeding frequency is also a measure of feeding practices and therefore one of our outcome variables. We will assess the feeding frequency of HIV-positive children by asking the caregivers to recall the number of times they fed their children in the 24 hours preceding the interview. WHO recommends feeding frequency of five times per day for HIV-positive children [19]. We will consider a feeding frequency of below five to be a low feeding frequency.

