Total training duration 13 hours 40 minutes.

According to the requirements set by the training guide, we will select trainers who are experienced in teaching the IMCI guide, managing undernutrition and HIV/AIDS among children, counseling, and recommending feeding practices for children [19]. We will include one pediatrician, one nutritionist, and one psychologist in the team of trainers. They will be provided with the trainer’s guide and the participants’ guide, as well as the booklet that comes along with the other training materials [19].

The trained MLPs will provide nutrition counseling to caregivers and will separately undertake direct measures for managing undernutrition to the HIV-positive children attending the CTCs of the intervention arm on a monthly basis for six months of the follow-up period. A similar intervention will be made available for the control group after evaluating the results.

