#### Follow-up

We will follow-up both intervention and control groups for 6 months. We will evaluate feeding practices, such as feeding frequency, dietary diversity, and quality and quantity of food eaten by children, as well as nutrition status, on a monthly basis for six months. For the intervention arm, we will also measure nutrition knowledge of MLPs before the training, immediately after the nutrition training, and again after the six-month observation period in order to measure the degree of knowledge decay.

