#### Quantity of food and quality of food

Amount and quality of food consumed by a child is again one of the measures of feeding practices and therefore an outcome variable in our study. We will measure food quality (ingredients or composition) and quantity using Tanzania food composition tables [29]. Such food composition tables provide information on calories, protein, vitamins, and essential minerals per 100 g of the local food type.

Adequate energy intake for HIV-positive children with no infections or severe undernutrition is 10% more than the requirement of normal children of the same age [19]. For HIV-positive children with opportunistic infections, energy requirements are 20% to 30% above normal children of the same age [19]. HIV-positive children with severe undernutrition have energy requirements of 50% to 100% above the required energy intake of HIV-negative children of the same age [19]. We will estimate the foods consumed in the previous 24 hours and work out specific ingredients. We will measure the amount consumed using common feeding utensils, such as plates, bowls or cups. We will categorize the diet as being low quantity if the child consumed an amount below the recommended value for that age.

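### Feeding practices are reported after the event, explicitly or by inference by caregivers counselled monthly in one arm only, so differential reporting can pass for improved feeding

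*Protocol article*

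**What the plan says.** The Measurements section describes three feeding measures.

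- **Feeding frequency** comes from "asking the caregivers to recall the number of times they fed their children in the 24 hours preceding the interview". The cut-off is stated as "We will consider a feeding frequency of below five to be a low feeding frequency", and five feeds a day is given there as the WHO recommendation.
- **Dietary diversity** is scored "from a recalled list of food items consumed over the previous day", against a set list of 12 items.
- **Quantity and quality of food**: "We will estimate the foods consumed in the previous 24 hours and work out specific ingredients", and "We will measure the amount consumed using common feeding utensils, such as plates, bowls or cups". This section does not say who supplies the information.

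Under Intervention, "The trained MLPs will provide nutrition counseling to caregivers", monthly for the six months of follow-up. The Abstract places this counselling in the 8 intervention CTCs, and the section on caregivers says that it is directed at them. Control CTCs are offered a similar intervention only after the results are evaluated.

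Under Follow-up, "We will evaluate feeding practices, such as feeding frequency, dietary diversity, and quality and quantity of food eaten by children", together with nutrition status, monthly for six months in both arms. Data analysis lists nutrition status and feeding practices as the two types of outcome and does not rank one below the other.

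**The concern.** For feeding frequency and dietary diversity, the person who reports the outcome is the person who receives the counselling. Quantity and quality very probably have the same source: they are retrospective, and children must attend with a caregiver to be included. Ordinary recall error would affect both arms alike. Here one arm is repeatedly taught what good feeding looks like, so any tendency to give the taught answer would run mainly towards benefit.

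The five-feed cut-off is the recommendation of the same WHO guideline on which the training is built. Table 1 includes sessions on the child's nutrition needs, what the child eats, who feeds the child and how.

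Improving feeding practices is a main objective, and the Discussion says that the findings could support scale-up. Because the two outcome types are unranked, a positive feeding result could be claimed on its own. The article describes no check on the recall, such as observed or weighed intake.

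**Working it through.** The plan has no figure of its own for this point. Its sample size (24 per cluster × 8 clusters = 192 per arm) concerns weight gain. What follows is an illustration under assumptions.

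**Inputs from the protocol article**
- 8 CTCs per arm and 400 children planned per arm, so 400 / 8 = 50 per CTC.
- ICC 0.01, which Sample size estimation assumes for weight gain.
- Low feeding frequency means fewer than five feeds.

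**Assumed inputs, not in the documents**
- True proportion below five feeds p = 0.50 or 0.60, equal in both arms (no true change).
- Share r of low-frequency intervention caregivers who report five or more: 0.10, 0.20 or 0.30. Control caregivers do not misreport.
- ICC 0.05 as a second value, because none is given for reported feeding.
- Two-sided 5% test with t on 16 − 2 = 14 df (critical value 2.145).

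**Formulas**
- Observed intervention proportion: q = p(1 − r). Spurious difference: d = p − q = pr.
- Design effect: DE = 1 + (50 − 1) × ICC, which is 1.49 at ICC 0.01 and 3.45 at ICC 0.05.
- SE = √{[p(1 − p) + q(1 − q)] × DE / 400}.
- Probability of a significant apparent benefit: upper tail of the non-central t with 14 df and non-centrality d / SE.

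**Worked case: p = 0.50, r = 0.20, ICC 0.01**
- q = 0.40 and d = 0.10.
- SE = √[(0.25 + 0.24) × 1.49 / 400] = 0.0427.
- d / SE = 2.34, which gives a probability of 59%.
- Odds ratio (0.40 / 0.60) / (0.50 / 0.50) = 0.67.

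**All cases**

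| p | r | q | Spurious difference (points) | Odds ratio | ICC 0.01 | ICC 0.05 |
|---|---|---|---|---|---|---|
| 0.50 | 0.10 | 0.45 | 5 | 0.82 | 19% | 11% |
| 0.50 | 0.20 | 0.40 | 10 | 0.67 | 59% | 30% |
| 0.50 | 0.30 | 0.35 | 15 | 0.54 | 91% | 59% |
| 0.60 | 0.10 | 0.54 | 6 | 0.78 | 26% | 14% |
| 0.60 | 0.20 | 0.48 | 12 | 0.62 | 74% | 41% |
| 0.60 | 0.30 | 0.42 | 18 | 0.48 | 98% | 74% |

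With no misreporting, the chance of a significant result in this direction would be 2.5%. A normal approximation in place of t on 14 df gives similar values: at p = 0.50 and ICC 0.01, 21%, 64% and 94% for shifts of 5, 10 and 15 points.

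**The case against.** **The sizes are assumed.** Nothing in the article supports a particular misreport rate or prevalence, and ICC 0.01 is the value that makes the problem look largest. This stands. The table is therefore given at two ICCs and shows what could happen, not what to expect.

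**Much of a sound procedure may already be planned.** Data collection provides trained research assistants, and nowhere are MLPs or CTC staff assigned the outcome interviews. Visit order is detail that an article can leave to the full protocol. This also stands in part: the article does not say that recall follows counselling, and its silence is not an error. The point rests on what is stated, namely the recall method, the one-arm counselling and the unranked outcomes.

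**The method has precedent.** The diversity score was used in earlier studies of HIV-positive children in Tanzania. That supports the instrument, but it does not address reporting that differs between counselled and uncounselled arms.

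**Stronger readings are not supported.** A reader might infer that every feeding outcome is stated to be caregiver recall; for quantity and quality that is an inference. A reader might also infer that caregivers are told to aim for five feeds; the article gives five only as the WHO recommendation and the cut-off. That learned answering grows with each session is plausible but not documented, and both arms become equally familiar with the questions. Finally, the trial as a whole is not exposed: underweight, wasting and stunting rest on measured weight and height, and the sample size rests on weight gain.

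**Conclusion.** The point holds for the feeding-practice outcomes only. Feeding frequency and dietary diversity are recalled, and quantity and quality are so by inference. Those reporting are counselled monthly in one arm, so a change in reported feeding cannot be cleanly separated from a change in what caregivers report.

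Under the stated assumptions, misreporting by one in ten low-frequency intervention caregivers would make a spurious benefit significant in 11-26% of trials across the two ICCs. At one in five the range is 30-74%, and at three in ten 59-98%. The true misreport rate is unknown, so these figures show vulnerability and do not predict a false positive.

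The change is worth making because it is cheap and the feeding outcomes can carry a claim alone.

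**What to change.** **Follow-up, and the Measurements sections on feeding.**
- At every visit in both arms, have the planned research assistants, not told the CTC's arm, complete the dietary recall before the caregiver sees the MLP that day.
- Use one open 24-hour recall of everything the child ate. Derive both the number of feeds and the 12-item diversity score from it afterwards, instead of asking for a count. The food-quantity measure already needs most of this information.

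**Data analysis.** Describe the feeding results as caregiver-reported. State that interview order removes same-day prompting but not answers learned at earlier visits.

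**What not to add.** Feeding claims should not depend on weight-for-age moving the same way. With no true weight effect, the estimate would point the favourable way about half the time. Trained MLPs also manage undernutrition directly, so weight could improve without a change in feeding. A real gain in diversity or frequency need not show in weight within six months.

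**Cost.** The interview is slightly longer and the feeding claim more cautious, with the same staff and visits. Some desirability bias will remain.
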